### Statistical analysis

All statistical analyses will be conducted using the IBM SPSS Version29.0.0.0 (Chicago, IL, USA). Variable distribution of similarity to normal will be assessed visually and using the Kolmogorov-Smirnov and Shapiro‐Wilk tests. Student’s t‐test, Mann‐Whitney test, and/or Wilcoxon rank test will be used for data comparison between groups. General Linear Modelling will be used for multiple dependent variables comparisons. Frequency, dependence, and homogeneity of statistical significance will be tested using the Chi square test, or/and Fisher’s exact test. The probability of equality will be tested using z‐test. Binary, multivariate logistic, linear, and nonlinear regression will be used to test correlations of the study findings adjusting for possible confounders.

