### Study procedure

The patients will be informed about the purpose and procedures of the study before signing the informed consent form. The breakdown structure of the study activities is presented in Fig. 1. A cardiologist will consult each patient about their eligibility to take part in the experiment, and their functional capacity will also be assessed. Following the consultation with the cardiologist, additional baseline assessments will be performed to evaluate demographic and clinical characteristics, weather sensitivity, Type D personality, subjective mental health status, and basal cortisol level. Basal cortisol level will be registered by testing cortisol concentration in saliva in the morning and in afternoon, one day prior to the experiment. After baseline measurements, patients will be randomly assigned to two groups: walking outdoors (OUT) or walking indoors (IN). OUT group will walk in the city park located within a 2–3 min walk of the LUHS NI Palanga Clinic along a pre-designated route. IN group will walk in a gym on a treadmill. The order and sequence of measurements within each trial will be the same (Fig. 2).

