### Experiment procedure

On the day of the experiment (Fig. 2), we will evaluate the effect of walking in different environments on hemodynamic parameters, stress level (according to cortisol concentration in saliva), and mood. In the morning, the patient will be fitted with a long-term blood pressure device, which will be removed the next morning. In this way, the patient will also receive detailed information about their hemodynamics. Both a collection of saliva samples and a mood assessment will be performed immediately before and after the intervention (walking). A cold pressure test (short immersion of patient’s hand into a cold container) will then be administered, followed by a third mood assessment. The third saliva sample will be collected 20 min after the cold pressure test. Cortisol levels rise progressively after a few minutes (about 10 min) of stimulation and peak between 10 and 30 min after stress termination [32, 33].

Participants in the OUT group will be instructed to keep a comfortable walking speed and to enjoy the walk and the surroundings. Participants in the IN group will be introduced to the treadmill and encouraged to choose a walking speed like that of leisurely outdoor walking. All participants will be informed that they will be accompanied by the researcher (at a distance) during the intervention to monitor their walking time, minimize the impact of social interaction, and control any potential well-being or health problems.

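### Only unadjusted tests are named for the between-arm comparison, none is fixed as primary, and the pre-walk values are not named as covariates in any analysis

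*Protocol article*

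**What the plan says.** The Statistical analysis section of the Protocol article gives each method a task.

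- It starts with distribution checks: "Variable distribution of similarity to normal will be assessed visually and using the Kolmogorov-Smirnov and Shapiro"-Wilk tests.
- For comparing the groups it lists Student's t, Mann-Whitney and/or, in its words, "Wilcoxon rank test will be used for data comparison between groups".
- "General Linear Modelling will be used for multiple dependent variables comparisons". No factors or covariates are given.
- Several kinds of "regression will be used to test correlations of the study findings adjusting for possible confounders". The confounders are not named.

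The Experiment procedure section sets out the measurements: "Both a collection of saliva samples and a mood assessment will be performed immediately before and after the intervention (walking"). It continues: "The third saliva sample will be collected 20 min after the cold pressure test". The Study procedure section adds a measurement from the day before: "Basal cortisol level will be registered by testing cortisol concentration in saliva in the morning and in afternoon, one day prior to the experiment".

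The Sample size section bases the trial on the cortisol response to stress, with Cohen d = 0.5 and power 0.95. It states a minimum of 82, doubled to 164 with 4% attrition in mind. It does not say whether the response is a raw value, a change or an adjusted value.

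**The concern.** A value of the outcome taken just before the intervention is usually the most useful covariate in a two-arm comparison. Here it is collected for cortisol and for mood in both arms, yet the tests assigned to the group comparison cannot use it as a covariate. Precision would be lost on the outcome that drives the sample size, and the result would be exposed to chance differences between arms before the walk.

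The choice of test is also open. A mean-based test and rank-based tests are joined by and/or, directly after normality checks, so the quantity being compared (means or ranks) may be settled only once the data are seen. The list is unclear in itself as well. Beside Mann-Whitney, a Wilcoxon rank test is either the same test again (rank-sum) or a paired test (signed-rank) that does not compare independent groups.

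**Working it through.** **Inputs from the document:** d = 0.5, power 0.95, minimum 82, planned N = 164, 4% attrition (164 × 0.96 = 157.4 completers), and equal arms from alternate allocation (82 per arm).

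**Assumptions:** alpha 5%, two-sided; d standardised to the SD of the raw outcome; equal SD before and after; r from 0.3 to 0.7. The Sample size section gives neither alpha, sidedness nor r.

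**The plan's own figure.** A two-sample t-test at d = 0.5 and power 0.95 needs 105 per arm, 210 in total (one-sided: 88 per arm, 176). With 82 in total, power is 0.61 two-sided and 0.73 one-sided. The stated 82 is therefore not reproduced. The nearest reading is 82 per arm, one-sided, with power 0.94; but the section treats 82 as the whole sample before doubling.

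**Effect size that each analysis sees** (n = 82 per arm, noncentrality = effect × √(n/2) = effect × 6.403):

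- raw post value: 0.5, so 3.20
- change score: 0.5 / √(2(1 − r))
- ANCOVA on the pre-walk value: 0.5 / √(1 − r²); at r = 0.5 this is 0.5 / 0.866 = 0.577, so 3.70

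**Power at N = 164:**

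| r | raw value | change score | ANCOVA | N for 95% with ANCOVA |
|---|---|---|---|---|
| 0.3 | 0.889 | 0.767 | 0.916 | 192 |
| 0.5 | 0.889 | 0.889 | 0.957 | 158 |
| 0.7 | 0.889 | 0.984 | 0.994 | 108 |

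The last column follows 210 × (1 − r²): 191.1, 157.5 and 107.1, each rounded up to an even number. With 157 completers, unadjusted power is 0.876.

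**Gain from ANCOVA over the raw comparison at 164:** 0.916 − 0.889 = 0.027; 0.957 − 0.889 = 0.068; 0.994 − 0.889 = 0.105.

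**Correlation needed for ANCOVA to reach 95%:** about 0.47 at 164, 0.50 at 158 and 0.78 at 82.

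**ANCOVA against a change score.** The ratio of variances is (1 − r²) / (2(1 − r)) = (1 + r)/2, which is below 1 for any r below 1. Apart from one degree of freedom, ANCOVA is at least as precise whatever r turns out to be.

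**The case against.** The strongest reply is that this is a journal article, no SAP is shown, and covariates and model formulas are commonly left to the SAP. That is fair for the details, and silence about covariates alone would not be a finding. But the article does not only stay silent: it assigns a particular set of tests to the group comparison, and a better method for that task is available from data already planned.

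Several stronger readings are tempting, and the document does not support them.

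- *The pre-walk value is discarded.* The text does not say so. The cortisol response could mean a change score, the linear model could cover the serial samples, and the regression could carry baseline cortisol. A change score does not repair the choice of analysis, though: at r = 0.3 it is worse than the raw comparison (0.77 against 0.89), and at r = 0.5 only equal to it.
- *Leaving out baseline costs the trial its stated 95% power.* That figure is attached to 82 patients, and an unadjusted test needs 210. The gap is mainly a sample-size error; adjustment would close it at 82 only with r of about 0.78.
- *The test is selected by normality tests.* This is the natural reading of the order of the sentences, but no rule is written. Without a rule, the effect on the error rate cannot be quantified.
- *Weather sensitivity is a stratum.* Allocation is plain alternation by order of consent, so it is not.

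It also stands that the size of the gain rests on an r that the document does not give, and that at r = 0.3 the gain is under 3 points. If d = 0.5 was meant on the change scale, the table does not apply directly. ANCOVA would then multiply the change-score variance by (1 + r)/2, that is 0.65, 0.75 and 0.85 at r = 0.3, 0.5 and 0.7.

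**Conclusion.** The point holds as a choice of method that should be improved. The only tests named for the between-arm comparison are unadjusted, no single one is fixed, and no baseline value is named as a covariate in any analysis. Under the stated assumptions (d = 0.5 on the outcome SD, two-sided 5%, N = 164), adjustment raises power from 0.89 to between 0.92 and 0.99 for r from 0.3 to 0.7. The direction of the gain does not depend on r; its size does. This is forgone precision and an open choice of test. It does not make the comparison invalid, and it does not explain the sample-size figure.

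**What to change.** State one primary between-arm analysis: an ANCOVA (the GLM procedure in SPSS, already the planned software) of cortisol in the sample after the cold test, on arm and pre-walk cortisol. Fix the scale in advance (for example log, reported as a ratio of geometric means with 95% CI) and alpha at two-sided 5%. Weather sensitivity may be added as a baseline covariate, but should not be described as a randomisation stratum. Use the same model for mood, with pre-walk mood as covariate. Do not choose the test from normality tests. Keep one named rank test for independent groups as a sensitivity check.

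The pre-walk sample is taken after assignment, though before the walk. A sensitivity analysis using basal cortisol from the day before would cover any effect of anticipation.

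Redo the sample size for this model with alpha, sidedness and the assumed r stated. The cost is wording and that recalculation: the change of analysis needs no new measurement or software.

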However, natural environments may not always be restorative, despite the fact that people tend to recover more quickly from stress and mental fatigue in natural than in urban settings [16]. In fact, physical environment can heighten or ameliorate stress, while meteorological factors also cause a certain stress on the human body [17]. Changes in meteorological parameters may affect human hemodynamics and other factors adversely, thereby catalysing the event of an acute coronary syndrome [18]. To this extent, little is known about the restorative or exacerbating potential of natural environments for weather-sensitive (WS) individuals. Concerning reactions to weather variations, people can be divided into two main groups: weather-resistant and WS [19, 20]. The term “weather sensitivity” is used to define the impairment of well-being and/or incidence of symptoms or exacerbations of diseases in response to weather changes [21]. According to the results of our earlier study, almost 50% of individuals with CAD described themselves as being WS [22].

WS profile and the effects of walking in nature on the psychophysiological stress response in individuals with CAD (WE_SENSE_THE_NATURE) is a pioneer study, aiming to investigate how weather sensitivity and walking in different environments affects psychophysiological responses to the stress of individuals with CAD during rehabilitation. The proposed randomised control trial will provide insight on the influence of environmental exposure, as it is seldom investigated in association to heart disease.

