### Randomisation

Depending on the date and time of consent to take part in the study, every second individual will be consecutively assigned to one of the conditions (e.g., the first individual will walk outdoors, the second will walk indoors, the third will walk outdoors, a fourth will walk indoors again and so on) without any prior preference or prioritization whatsoever.

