### Sample size

Based on previous research in this area [45], considering the cortisol response to psychophysiological stress as a primary approach to detect a likely medium difference between groups effect (Cohen d = 0.5) and achieve sufficient power1 (1-ß err prob = 0.95) requires a sample of at least *n* = 82 subjects. Considering possible side variable of weather sensitivity and differences in natural conditions, likelihood of 4% attrition, the sample is planned to be doubled to *N* = 164 subjects. The enrollment duration - one year.

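### Alternation over a one-year enrolment balances season between OUT and IN, but the named two-sample tests do not use that balance; if season affects the outcome, some precision is lost

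*Protocol article*

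**What the plan says.** - **Allocation.** Under Randomisation, "every second individual will be consecutively assigned to one of the conditions", in order of date and time of consent. The sequence is strict alternation, starting with OUT.
- **Calendar span.** Under Sample size, "The enrollment duration - one year", which is one full seasonal cycle.
- **Premise about weather.** The Background holds that "meteorological factors also cause a certain stress on the human body" and that weather changes may act on haemodynamics. Sample size gives differing natural conditions as one of the reasons for doubling the sample from 82 to 164.
- **Between-group tests.** Statistical analysis lists Student's t-test and Mann-Whitney, and/or "Wilcoxon rank test will be used for data comparison between groups". No pairing, block or time term is attached.
- **Other models.** The same section adds that "General Linear Modelling will be used for multiple dependent variables comparisons", and that binary, multivariate logistic, "linear, and nonlinear regression will be used to test correlations of the study findings adjusting for possible confounders". Neither sentence lists factors or covariates, and neither is said to be the OUT v IN test.
- **Sizing quantity.** Sample size works from "considering the cortisol response to psychophysiological stress as a primary approach", with d = 0.5 and "1-ß err prob = 0.95".

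**The concern.** Strict alternation acts like blocks of two in calendar time: each outdoor walker has an indoor neighbour from about the same date. A seasonal component common to both arms therefore contributes almost nothing to the error of the OUT-IN difference. An ordinary two-sample test does not know this. It estimates its standard error from the spread of all outcomes within each arm over the year, and that spread includes season.

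What is at stake is efficiency. If season matters, the test rejects less often than its nominal level under the null, its intervals are wider than they need be, and precision that the allocation has already secured goes unused. The protocol answers varying natural conditions with more patients, although the date of each experiment is known and could go into the model at no extra measurement cost.

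**Working it through.** **Inputs.** From the protocol: 164 patients, hence 82 per arm under alternation; one-year enrolment; d = 0.5 (outcome SD = 1). Assumed, because the protocol does not state them: two-sided 5% level; patients spread evenly over the year; seasonal share of outcome variance, R², from 0 to 0.30.

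**The plan's own figure.** The stated 82 is not reproduced. A two-group comparison at d = 0.5 and power 0.95 needs 105 per arm (two-sided t-test) or 88 (one-sided). With 82 per arm, two-sided power is 0.89. This is a separate matter, but it sets the starting power used here.

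**Standard error that the t-test reports.** It pools all variance:

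SE = √(2/82) = 0.1562, whatever R² is.

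**True SD of the OUT-IN difference under alternation, season common to both arms.** The seasonal part cancels:

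SD = √((1 − R²) × 2/82), so SE/SD = 1/√(1 − R²).

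**Consequences (normal approximation).** The t-test rejects when the difference exceeds 1.96 × 0.1562 = 0.306 in absolute value.
- Type I error = 2 × [1 − Φ(1.96 × SE/SD)]
- Power, unadjusted = Φ((0.5 − 0.306)/SD)
- Power, with season in the model = Φ(0.5/SD − 1.96)

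| R² | True SD | SE/SD | Type I error, t-test | Power, t-test | Power, season modelled |
|---|---|---|---|---|---|
| 0 | 0.1562 | 1.000 | 5.0% | 0.893 | 0.893 |
| 0.10 | 0.1482 | 1.054 | 3.9% | 0.905 | 0.921 |
| 0.20 | 0.1397 | 1.118 | 2.8% | 0.917 | 0.947 |
| 0.30 | 0.1307 | 1.195 | 1.9% | 0.931 | 0.969 |

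The gain in power is 1.6, 3.0 and 3.8 points at R² = 0.10, 0.20 and 0.30.

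**Simulation check.** Trials of 164 alternated patients, with a yearly sinusoid and evenly or uniformly spread dates, agree. The SE is about 5%, 12-13% and 18-19% too large. Type I error of the t-test is about 3.6%, 2.8% and 2.0%. Power goes from 0.90 / 0.91 / 0.93 to 0.92 / 0.94 / 0.97 once month or annual sine and cosine terms are in the model, and type I error returns to about 5%.

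**Is alternation the cause?** Under simple random permutation of the same patients, the t-test was calibrated (SE/SD = 1.00 at R² = 0.10 and 0.30). So yes.

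**Season in OUT only.** SE/SD falls to about 1.02 (R² = 0.10) and 1.04 (R² = 0.30), and the power gain to roughly 0.5-2 points.

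**Cost if season has no effect.** Spending 11 more degrees of freedom moves power from 0.8893 (162 df) to 0.8890 (151 df). In simulation the month term cost under 0.2 points.

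**The case against.** **The size is not in the protocol.** This stands. No section gives a seasonal variance for cortisol, blood pressure or mood, and the Discussion itself calls the evidence on many environmental variables unclear. A reader might infer that the planned intervals are certainly too wide. The document does not support that: at R² = 0 there is no excess.

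**The sizing outcome is a response, measured within one day.** Saliva is taken before the walk, after it, and 20 minutes after the cold test. If change from the pre-walk value is analysed, a seasonal shift in level cancels and only seasonal variation in reactivity remains. This stands as a reason to expect the lower end of the range. However, the analysis section does not commit to a change score.

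**Weather reaches mainly the OUT arm.** This is plausible, since IN walks on a treadmill. The gain is then small, and an additive month term captures only part of an arm-by-season effect.

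**A general linear model and adjusted regression are already planned.** They leave room for a time term, and a covariate list may sit in an analysis plan that is not shown; the absence of that list is not the point here. The point is that the tests the protocol does name for group comparison ignore the allocation. Adjusting for confounders would not obviously bring calendar time in, because alternation has already balanced it.

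**The Wilcoxon test may be the paired signed-rank test.** That is possible, but no pairs are defined, and the tests named beside it are for independent groups.

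**Alternation may not survive.** The Abstract and Study procedure speak of random assignment. Under simple randomisation the overstatement disappears. Alternation also raises a concealment question, which is a separate issue that a time term does not address.

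**Conclusion.** The point holds in conditional form. Alternation over a year balances calendar time between the arms, and the named two-sample tests make no use of it. If season explains 10-30% of outcome variance in both arms (an assumed range), the standard error is about 5-19% too large, the true type I error is about 4% down to 2% instead of 5%, and about 2-4 points of power are given up at d = 0.5 with 82 per arm. The loss is smaller if season acts mainly in OUT or if change from the pre-walk value is analysed, and nil if season has no effect.

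It would be tempting to read this as an invalid or biased comparison. It is neither: the estimate is not shifted by a season effect common to both arms, and the error is on the conservative side. The priority is that of a cheap efficiency gain. The figures rest on a two-sided 5% level, even recruitment over the year, a smooth annual cycle and alternation carried out as written.

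**What to change.** In Statistical analysis, state that the OUT v IN comparison is a linear model (the general linear model already named) with arm, the pre-walk value of the outcome, and calendar month of the experiment day as a fixed block. Annual sine and cosine terms are an acceptable alternative that uses fewer degrees of freedom. The two-sample tests can remain as a supporting analysis. Keep the time term if alternation is replaced by blocked random allocation in consent order, because that would balance calendar time in the same way.

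**Cost.** One sentence and no new measurement, since the experiment date is known for every patient. The month block uses up to 11 of about 160 degrees of freedom, with a negligible power cost if season has no effect.

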11.	Cold pressure stress	Cold pressure test (CPT) [43]	CPT will be used to induce acute stress. Temperature and other environmental stressors are known to affect BP and heart rate. In this activity, participants will be performed the cold pressure test to demonstrate the changes in BP that follow an environmental stress. For cold stress, the subject will immerse his or her right hand in the ice-water bath (4 °C) to a point just above the elbow for 2 min. BP measurements will be obtained using a long-term BP device – the SOMNOtouch NIBP monitor on the wrist of the left hand at 0, 1, 2, and 4 min after the right hand will be removed from the ice-water bath.	Up to 8 min
12.	Pain intensity	Visual Analog Scales (VAS) [42]	After the CPT, study participants will be debriefed about the purpose of the study and the subjective measure of perceived efforts and perceived difficulty of the CPT will be collected by using VAS. The scales ranged from 0 (maximum difficulty/efforts) to 100 (minimum difficulty/efforts). VAS were chosen based on its applicability in experimental clinical studies and common use in combination with CPT [44].	Up to 1 min

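### If the repeated outcomes enter one SPSS General Linear Model, one lost sample removes the whole patient from it; a mixed model per outcome avoids this modest loss

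*Protocol article*

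**What the plan says.** Under Statistical analysis the protocol article fixes the software ("All statistical analyses will be conducted using the IBM SPSS Version29.0.0.0") and then the method: "General Linear Modelling will be used for multiple dependent variables comparisons". It does not say which GLM procedure is meant or which variables share a model. The same paragraph lists the t-test, the Mann-Whitney test and the Wilcoxon test for two-group comparisons ("Wilcoxon rank test will be used for data comparison between groups").

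The design yields repeated values of each outcome:
- Experiment procedure: saliva and mood before and after the walk, mood again after the cold test, and a third saliva sample 20 minutes after that test.
- Table 1, cold pressure test: blood pressure "at 0, 1, 2, and 4 min after the right hand will be removed from the ice-water bath".

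The Sample size section uses the cortisol response "as a primary approach to detect a likely medium difference between groups effect" of d = 0.5 at power 0.95, and says this "requires a sample of at least *n* = 82 subjects". It then doubles 82 to 164 for three reasons taken together: weather sensitivity, differences in natural conditions, and a "likelihood of 4% attrition".

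**The concern.** GLM is the only method in the paragraph that is suited to several correlated outcome values compared across arms, so the natural reading is GLM Multivariate or Repeated Measures. In SPSS both procedures analyse only patients who have every dependent variable in the model. This is a general property of the procedures, not something the article states. A tube with too little saliva would therefore remove that patient's two good cortisol values as well.

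Two things are at stake. The first is precision, because patients who attended and were measured are discarded. The second is bias. If the chance of a missing later sample depends on an earlier observed value of the same outcome, the complete patients are a selected group. A mixed model uses the earlier value and remains valid under that kind of missingness; the complete-case analysis in general does not.

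**Working it through.** **Inputs from the article:** d = 0.5, power 0.95, n = 82, N = 164, 4% attrition, two arms filled alternately (1:1), three cortisol samples on the experiment day.

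**Assumptions:** two-sided alpha 0.05 (neither alpha nor sidedness is given); independent loss with probability p per cortisol sample (no rate is given), shown from 1% to 10%, with 2-5% as the working range.

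**1. The plan's own figure.** A two-sample t-test with d = 0.5 and power 0.95 needs 105 per arm, 210 in total (one-sided: 88 per arm, 176 in total). Neither 82 nor 164 results. Among the repeated-measures ANOVA settings tried (f = 0.25), only a few come within 2 of 82, for example 84 with three measures at correlation 0, or 82 for a four-group interaction with three measures at correlation 0.3. The article states none of these settings. Power below is therefore computed directly for the number of patients analysed.

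**2. After attrition.** 164 × 0.96 = 157.4, so 157 patients.

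**3. Complete on three cortisol samples.** Retained number = 157.4 × (1 − p)³. Power is for a two-sample t-test at d = 0.5, two-sided 0.05.

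| p per sample | (1 − p)³ | complete patients | power |
|---|---|---|---|
| 0 | 1 | 157 | 0.876 |
| 1% | 0.970 | 153 | 0.867 |
| 2% | 0.941 | 148 | 0.856 |
| 5% | 0.857 | 135 | 0.822 |
| 10% | 0.729 | 115 | 0.757 |

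In the working range, 157 − 148 = 9 to 157 − 135 = 22 patients are discarded, and power falls by 0.876 − 0.856 = 0.020 to 0.876 − 0.822 = 0.054.

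**4. Scale against the attrition allowance.** Deletion alone removes more than 4% of patients once 1 − (1 − p)³ > 0.04, that is p > 1 − 0.96^(1/3) = 1.35%. This compares sizes only. Attrition counts patients who leave, and deletion removes patients who stayed.

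**5. Omnibus test or single contrast.** With 82 per arm the noncentrality for d = 0.5 is 0.25 × 82 / 2 = 10.25. Power is 0.889 on 1 df and 0.818 if the same noncentrality is tested on 2 df. The second figure is a floor, because a multivariate test has at least the noncentrality of any single contrast it contains. It illustrates why the cortisol contrast should be stated in advance; it does not estimate a loss in this trial.

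**The case against.** The strongest objection is that the article never says the repeated values go into one model. It names no GLM procedure, it lists two-group tests that take one outcome at a time, and it sizes the trial on a between-group difference in cortisol response, which could be analysed as a change score with less deletion. Missing-data handling and exact model specification are also commonly left to a full protocol or SAP. This stands in part: the point has to be conditional, and silence on missing data is no finding. But the article does choose a method and software for multiple dependent variables, and the usual use of that method is complete-case.

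A reader might go further in four ways that the article does not support.
- *The 4% attrition figure fails.* It does not follow. Attrition and incomplete records are different quantities, and 164 does not rest on the 4% alone: 82 / 0.96 rounds up to 86. Every scenario above stays above the stated 82. That gives little comfort, since 82 does not reproduce and 164 complete patients give power 0.889 rather than 0.95, but that is a separate matter.
- *Cortisol, mood and blood pressure will be pooled in one large model.* No section proposes this, so the losses it would imply should not be counted.
- *The result is biased unless values are missing completely at random.* This is too strong. If missingness depends only on arm, which is in the model, the arm contrast is not biased by it. If it depends on unobserved values, a mixed model is biased as well.
- *The loss rates are facts about this trial.* They are assumptions. Independence also gives a larger loss than positively correlated missingness, which is plausible when a whole session fails.

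**Conclusion.** The concern holds in a conditional and modest form. If the repeated values of an outcome are modelled jointly by SPSS GLM, the analysis is complete-case, and the attrition allowance does not cover the patients it discards. For cortisol, at an assumed 2-5% independent loss per sample, 157 patients become 148 to 135 and power goes from 0.88 to 0.86-0.82 (d = 0.5, two-sided 0.05). Bias is possible when missingness depends on observed earlier values that the analysis does not condition on; its size cannot be judged from the article. The point is worth acting on because a better method is available in the named software at almost no cost, not because the planned sample size collapses.

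**What to change.** In the Statistical analysis section, replace GLM for the repeated outcomes by a linear mixed model fitted separately to cortisol, mood and blood pressure (SPSS MIXED, REML, all available values), with arm, time, arm-by-time and weather-sensitivity terms. For cortisol, the outcome used for sizing, pre-state one 1-df contrast: the arm difference in the response after the cold test, naming the earlier sample from which that response is measured.

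The cost is a change of wording and of SPSS procedure. No extra patients, samples or visits are needed.
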